### Plans to give access to the full protocol, participant-level data, and statistical code {31c}

Access to the complete protocol anonymized participant-level dataset and statistical code will be granted in parallel with publication.

## Oversight and monitoring

### Composition of the coordinating center and trial steering committee {5d}

The principal investigator, investigators, research nurses, and user representatives will meet once a week (study coordination unit). Research nurses and the primary investigator will meet weekly during the study period. The nurses and social workers providing weekly patient follow-up will meet daily with research nurses to ensure that both clinical aspects and research are well coordinated.

### Composition of the data monitoring committee, its role and reporting structure {21a}

There will not be an independent data monitoring committee, but the study coordination unit will ensure safety, adherence to the protocol, quality of the study, and ethical conduct.

### Adverse event reporting and harms {22}

All grade 3 (severe) and grade 4 (potentially life-threatening) adverse events are considered serious adverse events and will be reported to the study coordination unit that will ensure that proper follow-up will be provided, and if there are linked severe adverse events and significant differences between the arms, the trial will be terminated. Some might have adverse reactions to physical exercises and people with limited experience with exercise can find exercise unpleasant [36]. Participating in trials with an exercise-based intervention increases the risk of non-serious adverse events but not serious adverse events [37]. For safety evaluation, all serious adverse events occurring during the trial follow-up period will be recorded. According to current treatment guidelines, all serious adverse events will be followed until resolution or a stable clinical endpoint is reached. The research group led by the principal investigator, [name] will decide if it is necessary to terminate the trial.

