###  Background and rationale {6a}

Substance use disorders are associated with unhealthy lifestyle choices, resulting in adverse social and health consequences [1, 2]. People with opioid use disorder have particularly high morbidity, reduced physical fitness and quality of life [3–5], and a higher risk of premature death [6, 7].

Physical activity is defined as any bodily movement produced by skeletal muscles, which requires energy expenditure. Exercise is planned, structured, repetitive, and intentional physical activity intended to improve or maintain physical fitness [8]. Exercise has been suggested as an adjunctive treatment strategy for people with substance use disorder [7], due to its positive effects on health, quality of life, and reducing the burden of substance use disorder patterns [9, 10]. People with opioid dependence receiving opioid agonist therapy (OAT) often have significant mental health problems and calls for improved mental and physical health assessment and patient care [11, 12]. Physical activity and exercise can be effective adjunctive treatment methods for reducing nicotine, alcohol, and drug use [7, 13, 14]. Still, we need more knowledge about the effects of exercise as part of OAT, and how to best integrate an exercise program into OAT [15]. Few studies have investigated the effects of an exercise program on OAT patients [16–21], and none of these are randomized controlled trials with power to assess effects. Results from these studies suggest that exercise interventions could be desirable on physical fitness [19], substance use [16], and quality of life [19]. However, the potential effect is uncertain. Further research on exercise intervention would therefore be beneficial [12].

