### Interim analyses {21b}

There will be weekly meetings between the research nurses and the investigators throughout the study period. The meetings will evaluate the progression of the trial and adverse events.

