### Ethics {24}

In the study, participation is not assumed to pose a substantial risk. However, blood collection might be unpleasant, and exercise can be exhausting. The regional ethical committee has approved the study (no. 155386 REK sør/øst C, dated 23.09.2020/05.04.2022). The study is also registered online at ClinicalTrials.gov identifier: NCT05242848. The trial will be conducted according to the Declaration of Helsinki and other international conventions, GCP, and GLP standards [38, 39]. Each participant will be required to provide written informed consent and assent.

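### Serious adverse events are defined by severity grade alone, so deaths, and any admissions for lower-graded events, are not covered by the stated definition

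*Protocol article*

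**What the plan says.** All the operative text is in the protocol article, Adverse event reporting and harms {22}.

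- **Definition and reporting:** "All grade 3 (severe) and grade 4 (potentially life-threatening) adverse events are considered serious adverse events and will be reported to the study coordination unit".
- **Recording:** "For safety evaluation, all serious adverse events occurring during the trial follow-up period will be recorded".
- **Follow-up:** "all serious adverse events will be followed until resolution or a stable clinical endpoint is reached".
- **Termination:** "if there are linked severe adverse events and significant differences between the arms, the trial will be terminated".
- **Expected harms:** citing earlier evidence, the section says that taking part in exercise trials "increases the risk of non-serious adverse events but not serious adverse events".

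Three other places bear on the point. Interim analyses {21b} says of the weekly meetings: "The meetings will evaluate the progression of the trial and adverse events". Ethics {24} says: "The trial will be conducted according to the Declaration of Helsinki and other international conventions, GCP, and GLP standards". Background and rationale {6a} describes people with opioid use disorder as having high morbidity "and a higher risk of premature death".

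Hospitalisation appears only as an exclusion criterion in Eligibility criteria {10}, not as a safety event.

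**The concern.** Severity is how intense an event is. Seriousness is what it led to for the patient. The section uses the first to define the second. Its scale stops at events that could threaten life, so the worst outcome has no place on it.

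Reporting to the study coordination unit, recording, and follow-up to resolution all run on this category. The termination rule sits in the same sentence as the definition. The abstract makes further scale-up depend on the programme being shown to be safe as well as effective, so the between-arm safety comparison carries weight. A category that does not clearly take in deaths, but does take in intense reactions without lasting consequence, is a poor basis for that comparison, above all in a population that the article describes as being at raised risk of early death.

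**Working it through.** No arithmetic applies: the documents give no rate of deaths, admissions or graded events. The check sets the text side by side.

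**Step 1. Is there another definition?** No other section of the article defines a serious adverse event, lists death or admission as a safety event, or commits to recording any other class of adverse event. The weekly meetings evaluate adverse events, but that sentence sets neither a definition nor a duty to record. Ethics {24} names GCP without stating a seriousness definition.

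**Step 2. Apply the stated rule to each kind of event.**

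| Event | Covered by the stated definition? | Stated commitment to report, record and follow up |
|---|---|---|
| Grade 4 event | Yes | Yes |
| Grade 3 event with no serious outcome | Yes | Yes |
| Event graded 3 or 4 that later proves fatal | Yes, through its earlier grade | Yes |
| Death with no earlier grade 3 or 4 event on record | No fatal grade is named | None |
| Admission for an event graded 1 or 2, if the scale allows one | No | None |

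The grading scale is not named, so it is unknown whether the last row contains any events.

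**Step 3. Is the category balanced between arms?** Under Intervention {11a}, the exercise arm is offered 2 sessions a week for 16 weeks (2 × 16 = 32 sessions), with intervals at a preferred exertion above 13 on the Borg scale. Controls are offered none. Intense exertional reactions are therefore likelier in the exercise arm. They are not confined to it: the 4-minute step test is scheduled at the assessment visits in Table 1 without distinction by arm, and section {11d} leaves controls free to exercise.

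**Step 4. Would another part of the plan show a death?** Not distinctly. Section {20c} replaces a missing primary outcome with the baseline value. The one-year outcome for adherence to opioid agonist therapy counts those still receiving it with recent follow-up, so a death would look like any other loss from treatment. There is no independent data monitoring committee {21a} and no independent audit {23}.

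**Step 5. Are the terms used consistently?** The definition, recording and follow-up sentences use *serious*. The termination sentence uses *severe*, which in the definition is the label of grade 3 alone. The text does not say whether the termination sentence means grade 3, grades 3 and 4, or all serious events.

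**The case against.** The strongest case on the other side has four parts.

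- **The rule includes; it does not exclude.** The sentence makes grade 3 or 4 sufficient for seriousness and does not say that nothing else qualifies. This stands. A reader might infer that under the plan a death is not a serious event; the documents do not support that. What they support is that the stated definition does not cover it.
- **GCP is adopted.** This suggests that leaving out deaths was not intended. But the article gives no GCP definition and does not say how the general commitment relates to its own explicit rule. The two sections are left unreconciled.
- **Staff would know.** A reader might infer that deaths would never reach the study coordination unit. The documents do not support that either. The unit meets weekly and staff meet research nurses daily {5d}, patients are seen almost daily {9}, and clinical data come from medical records {19}. Staff would probably learn of a death. None of this is a commitment to record it as a safety event.
- **The article condenses a longer protocol.** The grading scale and fuller safety detail may stand there, and their absence here is not a fault. But this article does not leave the definition out. It states one, and the one it states uses severity in place of seriousness.

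It would also be tempting to put a number on the deaths missed. The documents give no mortality figure, so none is claimed.

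**Conclusion.** The point holds as a mis-specified rule, not as evidence that deaths are excluded or will be hidden. The only stated definition of a serious adverse event is a severity grade, with no fatal grade and no outcome criterion, and the only events the article undertakes to record and follow are those it calls serious. Deaths as such, and any admissions for lower-graded events, fall outside the stated definition. Grade 3 reactions without a serious outcome fall inside it and are likelier in one arm.

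The rule applies to all 324 planned participants over the whole follow-up period, but the number of events affected cannot be derived from the documents. The admission part depends on an unnamed grading scale and is less certain than the part on deaths. The sample size and the primary analysis of psychological distress are not affected; what is at stake is participant safety reporting and the safety conclusion.

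**What to change.** 1. In section {22}, define a serious adverse event by outcome, whatever its grade, and include death and in-patient admission among the outcomes. State how this meets the GCP commitment in section {24}.
2. Record severity grade as a separate item, on a named scale that includes fatal events.
3. Reconcile *severe* and *serious* in the termination sentence, so that it is clear which events it refers to. Which trigger is right is for the investigators to decide.
4. Re-classify the events already recorded. This cannot recover events never captured, so also check the medical records that section {19} already uses for deaths and admissions since enrolment, in the same way in both arms. Section {26b} says that participants consented to review of their records.

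**Cost:** a wording amendment submitted to the ethics committee, some re-coding, one check of records, and a few more reported events. No extra visits are needed.

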**Discussion:**

Systematically integrating exercise programs for people receiving opioid agonist therapy could lead to a shift towards a stronger focus on health behaviors in outpatient care. Integrating exercise could benefit patient recovery and reduce disease burden. Further scale-up will be considered if the provided exercise program is safe and effective.

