### Study setting and participants {9}

Recruitment will take place in OAT outpatient clinics in Bergen and Stavanger, two of the four largest cities in Norway. The Department of Addiction Medicine at Haukeland University Hospital in Bergen and OAT clinic in Stavanger have adopted an integrated treatment and care model for patients receiving OAT. In Bergen, OAT outpatient clinics are established in each district. Staff are multidisciplinary and include a consultant as well as a doctor specializing in addiction medicine, nurses, social workers, and psychologists. The patients are followed up almost daily with an observed intake of the OAT medications, such as methadone and buprenorphine treatment [22]. Bergen has suburb-based outpatient clinics while Stavanger has one main central outpatient clinic in addition to one for the neighboring areas. Except that, they are mostly similar. The treatment model in Bergen and Stavanger is a good platform to test the integration of additional interventions aiming to improve the health of a vulnerable group and gather knowledge, which traditionally has been very difficult to reach [23].

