### Procedure for unblinding if needed {17b}

Not applicable. The research nurses know patient assignment.

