## Data collection and management

### Plans for assessment and collection of outcomes {18a}

In both control and intervention groups, the outcome measures will be collected in the OAT clinics through a structured interview and clinical assessments of the participants.

Research personnel with background as health professionals will perform the data collection. Data collection and follow-up will be given in line with Table 1 and Fig. 1.

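### The harms section expects exercise to raise non-serious events but commits to recording only serious ones for safety evaluation, so 'safe' should be confined to serious events unless grade 1–2 events are collected alike in both arms

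*Protocol article*

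**What the plan says.** All references are to the protocol article.

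- **Adverse event reporting and harms {22}** classes grade 3 and grade 4 events as serious, which by implication leaves grades 1–2 outside. It cites evidence that joining an exercise trial "increases the risk of non-serious adverse events but not serious adverse events", and continues: "For safety evaluation, all serious adverse events occurring during the trial follow-up period will be recorded". Reporting to the study coordination unit and follow-up to resolution concern serious events. The termination trigger concerns severe events with a difference between arms.
- **Abstract, Discussion**: "Further scale-up will be considered if the provided exercise program is safe and effective".
- **Interim analyses {21b}**, on the weekly meetings of research nurses and investigators: "The meetings will evaluate the progression of the trial and adverse events". No grade limit is given.
- **Outcomes measures {12}** and **Table 1** contain no adverse event item of any grade. Table 1 has a clinical assessment row at screening and at each later assessment, with its content not described.
- **Additional consent provisions {26b}** and **Data management {19}** allow review of medical records and the extraction of clinical data from them.
- **Study setting {9}** describes frequent contact: "The patients are followed up almost daily with an observed intake of the OAT medications".

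**The concern.** Two adjacent sentences do not fit together. One says which class of harm exercise is expected to increase. The next names a different class as the one recorded for judging safety. A comparison of serious events alone could look reassuring because the programme was never expected to change them, while the expected harm went uncounted.

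The sessions are outdoor uphill intervals at moderate or higher intensity plus resistance work, in patients the background section describes as having high morbidity and reduced fitness. Falls and musculoskeletal injuries below grade 3 are the plausible cost. They also bear on tolerability in a trial that assumes only 62.5% of the exercise arm takes active part. At stake is what the trial may conclude about safety, which the abstract makes a condition for considering scale-up.

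**Working it through.** The plan gives no adverse event rate, so there is no figure of its own to reproduce on this point. The first step is a comparison of texts; the arithmetic after it only gauges size.

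**1. Is grade 1–2 collection, alike in both arms, stated anywhere?**

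| Place | What it provides | Does it state grade 1–2 collection in both arms? |
|---|---|---|
| Harms {22} | Recording of grade 3–4 events | No |
| Outcomes {12} | Outcome list without adverse events | No |
| Table 1 | Clinical assessment row, content not given | Not stated |
| Interim analyses {21b} | Weekly review of adverse events, any grade | Review only; no recording by arm stated |
| Consent {26b}, Data management {19} | Access to medical records | Not stated; would show medically attended events only |
| Study setting {9} | Almost daily clinic contact | Contact, not recording |

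Informal notice may also be uneven. The exercise arm is supervised twice a week, where minor injuries can be seen; the control arm has no such sessions.

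**2. What serious events alone can support.** Input: 162 per arm (Sample size {14}), assumed fully followed. With 0 events the exact two-sided 95% upper limit is 1 − 0.025^(1/162) = 0.0225, or 2.3%. It applies to grade 3–4 events and sets no limit on grade 1–2 events.

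**3. How many end-assessments could still be changed.** Inputs: recruitment from 19 April 2022 to an estimated December 2023 (Trial status); publication on 29 February 2024. Assumptions: even recruitment, exercise starting at recruitment, assessment at week 16.

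- 29 February 2024 minus 16 weeks (112 days) = 9 November 2023.
- 9 November to 31 December 2023 = 52 days; 19 April 2022 to 31 December 2023 = 621 days.
- 52/621 = 8.4%, and 0.084 × 324 ≈ 27 participants, about 14 per arm.
- If recruitment ended on 1 December 2023: 22/591 = 3.7%, about 12 participants.

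**4. Precision of an added question, as illustration only.** The documents give no event rate; about 5–20% of participants per arm is assumed. The Newcombe 95% interval for the difference combines the Wilson limits (l, u) of each arm: the distance below the observed difference is √[(p₁ − l₁)² + (u₂ − p₂)²], and the distance above is √[(u₁ − p₁)² + (p₂ − l₂)²].

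- 162 per arm: 8 v 8 events gives ±5.1 percentage points; 32 v 32 gives ±8.7.
- 14 per arm: 1 v 1 gives ±25.0 points (Wilson limits 0.013 and 0.315 around 0.071, so √(0.0587² + 0.2433²) = 0.250); 3 v 3 gives ±29.6.

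The question would therefore have been informative if asked of everyone. On the stated schedule it adds little.

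**The case against.** The strongest reply is that this argues from silence in a condensed article. The harms section says that serious events will be recorded; it does not say that only they will be. The article refers to a fuller document ("Access to the complete protocol anonymized participant-level dataset and statistical code will be granted"), which may collect lower grades. The outcome list and Table 1 prove little, since they omit serious events too, although these are recorded. The unspecified clinical assessments, the medical records and the weekly meetings could all bring minor events to light. *Safe* occurs in one abstract sentence and is not a decision rule. Counting every grade 3 event as serious already catches severe injuries, and light recording is defensible where the ethics section assumes no substantial risk.

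Much of this stands. A reader might infer that non-serious events are not collected at all, or that the two harms sentences contradict each other. The documents support neither: one sentence reports background risk, and the other states what will be recorded without excluding the rest. The absence of an adverse event row in Table 1 cannot carry the point either.

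What does not fall is narrower. The article chose to name both the expected harm and the events recorded for safety evaluation, and the two do not match. None of the other routes is described as collecting grade 1–2 events in the same way in both arms, which a comparison would need.

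**Conclusion.** The point holds in limited form. On the article's wording, a conclusion that the programme is safe would rest on grade 3–4 events, the class not expected to rise, and would not cover the class that is.

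It is minor. The primary analysis of psychological distress is unaffected, serious events remain comparable by arm, and no stated stopping criterion changes. The conclusion rests on the absence of any statement that grade 1–2 events are collected alike in both arms. If the complete protocol provides for that, only the sentence in the harms section needs correcting. The figure of about 27 participants depends on the estimated recruitment dates and even accrual; the interval widths depend on assumed event rates and are not findings about this trial. It would go too far to say that the trial cannot assess safety, or that minor harms were ignored.

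**What to change.** 1. **Wording, possible at any stage before reporting.** If grade 1–2 events are already collected the same way in both arms, correct the harms section to say so. If not, add: *Conclusions on safety refer to serious (grade 3–4) adverse events only*, and qualify *safe* in the abstract likewise. Do not write that non-serious events were not collected unless the sponsor confirms it. Cost: one or two sentences and no data.

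2. **Any end-assessments still ahead (12–16 weeks).** The setting exists: "In both control and intervention groups, the outcome measures will be collected in the OAT clinics through a structured interview". Add one identical question in both arms on injuries and falls since randomisation, asked after the SCL-10 and the step test so that it cannot colour them. Limit it to injuries and falls; in a population with high morbidity, a question on any new complaint would largely pick up background illness. Report participants with at least one event per arm, and the difference with a 95% confidence interval.

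The cost of the second change is one question and a little data entry. Its downsides are imperfect recall over 12–16 weeks and self-report by unblinded patients to staff who may know the allocation ("The research nurses know patient assignment"), so part of any difference could be reporting. Few participants would be reached if recruitment closed in December 2023. On that schedule the first change is the one that matters; if recruitment was extended, the second is worthwhile.
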